## Abstract

**Background:**

Important evidence has been constantly produced and needs to be converted into practice. Professional consumption of such evidence may be a barrier to its implementation. Then, effective implementation of evidence-based interventions in clinical practice leans on the understanding of how professionals value attributes when choosing between options for dental care, permitting to guide this implementation process by maximizing strengthens and minimizing barriers related to that.

**Methods:**

This is part of a broader project investigating the potential of incorporating scientific evidence into clinical practice and public policy recommendations and guidelines, identifying strengths and barriers in such an implementation process. The present research protocol comprises a Discrete Choice Experiment (DCE) from the Brazilian oral health professionals’ perspective, aiming to assess how different factors are associated with professional decision-making in dental care, including the role of scientific evidence. Different choice sets will be developed, either focusing on understanding the role of scientific evidence in the professional decision-making process or on understanding specific attributes associated with different interventions recently tested in randomized clinical trials and available as newly produced scientific evidence to be used in clinical practice.

**Discussion:**

Translating research into practice usually requires time and effort. Shortening this process may be useful for faster incorporation into clinical practice and beneficial to the population. Understanding the context and professionals’ decision-making preferences is crucial to designing more effective implementation and/or educational initiatives. Ultimately, we expect to design an efficient implementation strategy that overcomes threats and potential opportunities identified during the DCEs, creating a customized structure for dental professionals.

**Trial registration:**

https://osf.io/bhncv.

**Supplementary Information:**

The online version contains supplementary material available at 10.1186/s12903-024-04090-3.

## Background

There has been a continuous production of important evidence that needs to be translated into practice. However, there is a gap between what is produced and what is practised [1, 2]. Translation of research into products, policies, and practices is estimated to take 17 years [2]. Traditional decision-making is entrusted to health professionals. It is a complex process that can be affected by many factors, such as those related to the patients (as socioeconomic status, patient age and gender), to the environment (resources available and geographic location), and to the professional itself (professional age, gender, work overload, family issues, beliefs, school philosophy) [3–9].

Although evidence-based practice has been widely recommended [10], the actual role of scientific evidence in decision-making and its relevance (or remains) when combined with other decisive factors is still unclear. Indeed, we do not properly know which attributes (e.g. costs, training, success rates, patients’ satisfaction) are considered by oral health professionals when choosing between options for caring for their patients. Professionals seem to use their own criteria to identify and compare/weigh the options [11]. Therefore, professional consumption of scientific evidence, especially recently produced, may hinder its implementation, increasing the time lapse between evidence production and its use in the real world. Then, implementation research should plan actions to change the beliefs and paradigms of these professionals [12] or customize their actions to offer the evidence in the “right” format for its potential consumers, improving the engagement of professionals with scientific evidence through knowledge translation initiatives.

Discrete Choice Experiments (DCEs) can be used to measure the value of each attribute (individual utilities) in choosing one alternative over others in clinical decision-making [13]. The preference for one given alternative over another depends on values built through knowledge, experience, and reflection [14]. A DCE is based on the random utility theory to measure the stated preferences of stakeholders. The preferences are measured by the valuation of attributes, which are characteristics that may influence the individual decision (e.g. colour). Each attribute is further defined by levels [15, 16], which are different manners of such characteristics appearing (e.g. green or red) (Fig. 1a). The attributes and their levels are combined in several possibilities to generate the profiles and tasks through the experimental design theory [17–19] (Fig. 1b). This study is pioneer using this methodology to understand dentists’ decisions and the actual weigh the scientific evidence represents on such regard.

**Fig. 1 Fig1:**
[figure not shown]
(**A**) Examples of different attributes which could interfere with a certain choice (e.g. color, size etc.). Each attribute is then defined by specific categories which caractherize them (they are named levels—e.g. for color—green or red; for size 30, 45 or 60 inches). (**B**) Example of paired choice combining different levels of different attribiutes in such experiment investigating the preference. Given a forced choice experiment, the respondent must have to choose one alternative even anyone is the perfect one for him/her. Then, they probably will choose one alternative which have the preferred levels of such attitbutes according to his/her opinion

Understanding the oral health professionals’ context and preferences captured through the attributes’ value may lead to informed planning of more relevant and effective implementation of evidence-based strategies in clinical practice by considering real-world data related to the consumption of evidence-based information. Consequently, we expect to improve the oral health professional’s compliance with clinical practice based on the current scientific evidence by maximizing strengthens and minimizing barriers related to that.

## Methods/Design

This protocol was written following the ISPOR Good Research Practices for Conjoint Analysis Task Force [15, 19], adjusted for a protocol (Additional file 1).

### Aim/Study Design

A cross-section DCE was designed to assess through the oral health professional’s perspective whether the available scientific evidence supporting a clinical alternative is considered in the decision-making process and how it is combined with other factors such as costs, patient needs, and/or dental associations or experts’ recommendations. Hypothetical situations will be created. Additionally, we intend to explore professionals’ preferences and choices associated with different interventions proposed in pediatric dentistry and supported by scientific evidence recently produced. Finally, we will check if labelling the options may influence professionals’ decisions despite the preferred attributes chosen in non-labelled alternatives. Due to these different aims, the experiment will be divided into different stages to contemplate each of the mentioned aims, and a specific DCE instrument will be designed for that.

### Research question and hypothesis

To satisfy the aims above, we defined two main research questions: (1) What is the relative importance of scientific evidence in oral health professionals’ decision-making? (2) What are the trade-offs between attributes involved in the decision to adhere to an evidence-based new clinical practice (intervention or diagnostic strategy which are not yet usual to professionals but recently fomented by scientific evidence).

### Participants

Our sample will comprise Brazilian oral health professionals who agree to participate in the study. As the application will be through an online platform, those who do not have access to a device such as a smartphone, tablet, computer and/or do not have access to the internet will not be able to participate.

The recruitment strategy will target dentists from both the public and private sectors. Health Departments from different states in Brazil will be contacted as facilitators to organize an application day for the public sector. Local events (congresses and commercial meetings) will be used to recruit participants from the private sector. Participants enrolled in this study will be invited to become citizen researchers and, after a training, apply the same instrument to their peers (other dentists) in their community. This approach will be used to achieve participants from different parts of Brazil and not only those who are close to research centers [20, 21].

Participants who consent to become citizen researchers will receive training to calibrate them both in ethical aspects and methodological aspects, guaranteeing the integrity and autonomy of the participants who will be recruited by them as well as the scientific confidence and rigor of the data collected [20, 22]. Individual and collective targets will be defined for the citizens research considering the number of dentists supposed to be achieved with this strategy of citizen science. A monitoring platform will be created [23] to motivate data collection and establish communication between investigators and citizen researchers.

The sample size will be calculated based on an arbitrary rule summing up 10 respondents for each attribute defined for the DCE and extra 50 participants [24]. By anticipating a maximum of six attributes in the experiment, we expect that a sample of 110 respondents would be needed to provide sufficient statistical power based on the rule described above. An additional number of participants will be increased in sample size for compensating possible a 20% non-respondent rate, totalizing an anticipated minimum sample of 132 dentists. After defining the attributes, this calculation will be adjusted, if necessary.

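### The stated minimum of 132 dentists does not cover the 20% non-response it is meant to offset: it leaves about 105.6 respondents against the 110 required, and 138 would be needed

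*Protocol article*

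**What the plan says.** All the figures are in the Participants section of the protocol article.

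- The rule for the sample size is "summing up 10 respondents for each attribute defined for the DCE and extra 50 participants".
- The attribute count put into it is an upper limit: "By anticipating a maximum of six attributes in the experiment".
- The result is given as a number of respondents: "we expect that a sample of 110 respondents would be needed to provide sufficient statistical power".
- Participants are then added, with the purpose and the outcome given together: "compensating possible a 20% non-respondent rate, totalizing an anticipated minimum sample of 132 dentists".
- The paragraph closes with a provision for revision: "After defining the attributes, this calculation will be adjusted, if necessary".

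**The concern.** The requirement of 110 counts people who respond. The 132 counts dentists in the sample before non-response. The paragraph presents the second figure as the one that secures the first when one dentist in five does not respond. That holds only if 80% of 132 is at least 110, and it is not.

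What is at stake is modest but concrete. The protocol states a minimum that, under its own assumption, does not reach its own requirement. The same section says that targets for the citizen researchers will be set with the number of dentists to be reached in mind, so a total that is too low could pass into those targets.

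**Working it through.** **Inputs, all from the Participants section**

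- Rule: 10 respondents per attribute, plus 50
- Attributes: 6 (anticipated maximum)
- Non-response rate: 20%
- Stated minimum sample: 132

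Significance level, power and effect size do not enter, because the size comes from a rule of thumb.

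**Step 1: reproduce the plan's figures**

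- Required respondents: 10 × 6 + 50 = 110. This matches.
- Multiplying by one plus the rate: 110 × 1.20 = 132. This matches exactly.
- Dividing by one minus the rate: 110 / 0.80 = 137.5, rounded up to 138. This does not match 132.

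The protocol prints no inflation formula, but 132 agrees with the first operation and not with the second.

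**Step 2: what 132 delivers at the stated rate**

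- Expected respondents: 132 × (1 − 0.20) = 105.6
- Shortfall: 110 − 105.6 = 4.4 respondents, or 4.4/110 = 4.0%
- Non-response that 132 can absorb: 1 − 110/132 = 16.7%

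**Step 3: what the stated rate requires**

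- 110 / 0.80 = 137.5, so 138 dentists
- Check: 138 × 0.80 = 110.4, which meets 110
- Difference from the stated figure: 138 − 132 = 6 dentists

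**Step 4: does the error depend on the attribute count?**

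Multiplying by 1.20 and then losing 20% leaves 1.20 × 0.80 = 0.96 of the requirement, so the 4% shortfall arises at any count.

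| Attributes | Respondents required | × 1.20 | Respondents left at 20% | ÷ 0.80, rounded up |
|---|---|---|---|---|
| 4 | 90 | 108 | 86.4 | 113 |
| 5 | 100 | 120 | 96.0 | 125 |
| 6 | 110 | 132 | 105.6 | 138 |

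**Step 5: chance of reaching 110**

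This step adds an assumption that is not in the protocol: dentists respond independently, each with probability 0.80. The probability of at least 110 respondents is then about 0.20 from 132 dentists and about 0.58 from 138. Even 138 secures the requirement only on average, which is what an allowance of this kind normally aims at.

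**The case against.** The strongest defence is that little turns on the difference, and that the text leaves room to absorb it.

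- **The 132 is an anticipated floor with no stated cap.** True, and recruitment may exceed it. But a minimum is the figure that should suffice by itself, and at the stated rate this one does not.
- **Six attributes is a maximum.** This stands as a limit on the point. With five attributes the requirement is 100, and a sample kept at 132 would meet it with 105.6 expected respondents.
- **The calculation may be adjusted later.** The adjustment is tied to the attribute list, not to the non-response step, so it does not repair the figure.
- **The 20% may simply mean 20% extra.** That explains where 132 came from. The text, however, calls it a non-respondent rate to be offset, and 20% extra does not offset a 20% loss.
- **Missing data will be imputed** (Data Collection section). Imputing variables does not turn non-respondents into respondents under a rule that counts respondents.

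A reader might infer three stronger things, and the document supports none of them.

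- *That the study will be underpowered, or that the power wording is a separate error.* The protocol openly calls its rule arbitrary and ties the power wording to that rule. The attributes, levels and number of choice tasks are not yet fixed, so any detectable effect would rest on invented design values. An analysis plan is also said to exist elsewhere and is not shown.
- *That six more people must be invited.* The sample is defined as professionals who agree to take part, so the count is of dentists in the sample, not of invitations.
- *That the same multiplication will be used again.* That is a risk, not a stated plan.

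**Conclusion.** The stated minimum is wrong as written. At 20% non-response, 132 dentists give an expected 105.6 respondents, 4 to 5 below the required 110, and 132 tolerates 16.7% rather than 20%. The figure consistent with the protocol's own inputs is 138.

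This rests on two readings: that 110 is a number of respondents, which the text says directly, and that the 20% is a share of the sampled dentists, which is the ordinary meaning of a non-response rate. It applies at six attributes, the anticipated maximum.

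The shortfall is about 4% of a threshold that comes from a rule of thumb. Nothing in the document makes a test or decision depend on 110 rather than 106, so the point is a figure to correct and not a threat to the study's conclusions.

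**What to change.** Either of two changes to the Participants section is enough:

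1. Restate the minimum as 138 dentists, showing 110/(1 − 0.20) = 137.5, rounded up.
2. Keep 132 and state that it yields about 105 respondents at 20% non-response, or equivalently that it tolerates non-response of up to 16.7%.

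In both cases, state that any recalculation after the attributes are defined will divide by (1 − 0.20). With five attributes that gives 100/0.80 = 125, not 120. Any recruitment targets for citizen researchers derived from the total should use the corrected number.

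The cost is one figure and one sentence. The first option adds six dentists to the sample; the second adds none and makes a slightly less favourable statement.

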### Settings

The DCE instrument will be self-administered and delivered in a virtual environment. The computerized approach has already been used in previous studies measuring preferences [25]. This strategy is also reported as an alternative by the World Health Organization guidelines for conducting DCEs [26].

### Instrument properties

The template (electronic form) to be responded by the participants will include the Informed Consent Form, a preliminary questionnaire to capture participants’ information, and the DCE instrument by itself, containing the choice sets defined according to the steps described in the next sections.

The questionnaire will collect participants’ data such as gender, age, position (dentist, manager, coordinator), place of residence and work (Federative Unit of Brazil), year of graduation, and graduate courses (completed or not).

The DCE instrument will consist of two choices-sets with pairs of unlabeled alternatives (binary forced-choice experiment). Each choice-set comprises a different clinical decision context (Fig. 2).

**Fig. 2 Fig2:**
[figure not shown]
Two main choice sets and hypothetical factors that potentially affect the dentists’ decision

The first one will focus on understanding the role of the attribute “scientific evidence” in the decision-making process. An experimental design will be created by combining different levels of attributes, resulting in hypothetical alternatives to measure that. The other set will focus on understanding specific attributes considered for choosing diagnostic and therapeutic interventions when such a decision is required in clinical practice. The interventions considered were related to caries diagnosis strategies and minimally invasive interventions. This set will be divided into three stages: (a) hypothetical alternatives combining levels of attributes, as the first set; (b) real alternatives, non-labelled, including the same attributes whose levels will be defined by pairs of interventions sourced by well-designed randomized controlled trials in the Brazilian context (Table 1), (c) the same alternatives from item “b”, but labelled. In this second set, the labelled and non-labelled alternatives (items “b” and “c”) will be displayed randomly to avoid generating an automatic association between them.

**Table 1 Tab1:** Newly scientific evidence. Brief description of the randomized controlled trials that will be used to guide the DCE-interventions instrument, detailing the conditions and interventions tested in each of them

NCT or REBEC (PMID)*	Condition	Age (n)	Intervention group	Control Group	Follow-up (months)	Primary outcome	Secondary outcomes
02078453 (32,450,979)	Caries lesions detection and diagnosis^**(1)**^	3–6 (252)	Visual Inspection	Visual Inspection and bite-wing radiographs.	24	Surfaces with operative treatment needed	• New carious lesion; • Repairs needed; • Pain episodes; • Extractions; • Oral health-related quality of life • Economic
02473107 ( - )	Initial carious lesions detection ^**(2)**^	3–6 (260)	Detection and treatment based on all lesions severity	Detection and treatment based on advanced carious lesions	24	Surfaces with operative treatment needed	• Economic • Discomfort • Oral health-related quality of life
03520309 (32,615,237)	Carious lesions associated with restorations ^**(3)**^	3–10 (550 restorations)	Caries Around Restorations System (CARS) and International Caries Classification and Management System (ICCMS)	International Dental Federation (FDI)	24	Restorations with operative intervention needed.	• Restorations survival; • Repair needed; • Restoration substitution needed; • Carious lesion associated with restorations; • Pul inflamation symptons; • Economic; • Oral health-related quality of life.
02274142 (34,301,217)	Restorations survival^**(4)**^	3–10 (324 restorations)	Encapsulated GIC (Equia Fill®, GC Europe)	Hand-mixed GIC (Fuji IX®, GC Europe )	24	Restoration survival	• Economic
02789202 ( - )	Non-frankly cavitated carious lesions^(5)^	1–3 (100)	Silver Diamine Fluoride	Fluoride varnish	24	progression to dentin carious lesions	• Patient’s acceptability (VAS scale) • Economic
02569047 (33,176,756)	Occluso-proximal carious lesions^**(6)**^	5–10 (131)	Hall Technique	Atraumatic Restorative Technique	36	Restoration survival	• Discomfort • Patient’ acceptability • Occlusal Vertical Dimension • Oral health-related quality of life.
03005405 ( - )	Moderate carious lesion^**(7)**^	3–6 (101)	GIC sealant	GIC Restoration	24	Reintervention needed	• Discomfort • (Wong-Baker scale) • Economic
02377297 (32,758,684)	Restoring occlusal dentin caries lesions in primary molars [8]	4–8 (150)	Vitro Molar (nova DFL)/ Maxxion R (FGM)	Fuji IX Gold Label (GC Corp)	24	Restoration survival	• DMFT • Economic

NCT—Number ClinicalTrials.gov.

N—Sample Size.

GIC—Glass Ionomer Cement.

DMFT - Decayed, Missing due to caries, and Filled Teeth.

VAS—Visual Analogue Scale.

REBEC - The Brazilian Clinical Trials Registry / Registro Brasileiro de Ensaios Clínicos.

2. Martins IFN. Impacto da detecção de lesões iniciais e da avaliação da atividade de cárie em dentes decíduos: estudo controlado randomizado (CARDEC-02) com 1 ano de seguimento: Universidade de Sâo Paulo; 2017.

**Fig. 3 Fig3:**
[figure not shown]
The flow of development of the Discrete Choice Experiment instrument

### Instrument development

The development of the DCE instrument was divided into four phases: 1-definition of attributes and levels; 2- determination of the experimental design (efficient combination of the attributes and attribute levels presented to the respondents), 3- pilot test of the preliminary instrument and 4-adjustments in the preliminary instrument to create the final version of the instrument to be used in the experiment (Fig. 4) [15, 19]. Each one of these phases will be detailed below.

**Fig. 4 Fig4:**
[figure not shown]
Presentation of sequential questions (A to B) with the scenario and hypothetical unlabeled alternatives. Note that when answering question A, question B is presented, varying hypothetical attributes “patient acceptability” and “cost”

Phase 1: **Definition of attributes and levels**—A non-systematic literature search will be performed, looking for all possible factors associated with the professional’s clinical decision-making (choice set 1) and related to specific interventions from Table 1 (choice set 2). Afterwards, a discussion in the research group will be guided to generate a comprehensive primary list of all potential attributes and their variation in potential levels for each choice set. Then, a multidisciplinary panel will be formed, including stakeholders from different Brazilian regions, aiming to guarantee national representativeness for discussing and finally defining the definitive list of attributes and levels. Ideally, the panel will comprise the following representatives: dentists who work in private clinical practice, dentists who work in public practice, undergraduate students, health service managers, researchers who work with knowledge translation, researchers who work with evidence-based practice, and opinion leaders in Dentistry. The preliminary list with all attributes and their levels, definitions, justification, and references for each attribute will be presented, and a discussion will be opened regarding the range of levels, understanding of the attribute, and whether other attributes should be added. Besides, suggestions to reformulate levels and attributes should be accepted.

The multidisciplinary panel will be recorded, and a qualitative thematic analysis [27, 28] will be performed to explore further possible differences in the discourses of selected stakeholders and the respondents’ views. The discussion will be verbatim transcribed using the voice typing tool from Google Docs [29], and the authors of the speeches will be anonymized for the publication and dissemination of the results. An independent investigator will be invited to carefully read the transcripts while hearing/watching the recording to ensure that the transcription was completed in full. Qualitative data analysis will be described further.

By the end of the panellist discussions, the coordinator board ([name], [name], [name], [name], [name]) will be gathered to refine the list generated, preserving the previously given contributions. The final attributes and levels list will be finally sent to all panellists, and each level’s approval rate will be registered. To be approved, final levels and attributes must be approved by the most representatives in the panel (at least 80% of approval). If this approval rate is not achieved, all panellists’ views about such a specific disapproved level will be reconsidered.

Phase 2**—Determination of the experimental design**—At this stage, the aim was to produce a number of pairs of alternatives, combining the levels of the attributes. The experimental design is a manner to combine these pairs for each choice set in the most efficient arrangement of the pairs of alternatives, aiming not to use all possible combinations (cognitively impossible), but a number enough to permit the preference to be measured. The more attributes and levels (more sets of choices) used, the greater the complexity of the experiment and, consequently, the more significant unobserved variability we must consider in the analysis [18]. A list with minimum but enough combinations will be generated at the end. We will exclude alternatives with implausible combinations of unbalanced choice levels and sets to adjust the experiment, ensure the plausibility of the choices, and reduce hypothetical bias (when the hypothetical nature of the questions results in biased answers). The design efficiency (Efficiency D) will be calculated to determine if the number of pairs can assess the possible effects (preference) intended to be measured. These calculations will be performed using the Ngene software [17, 19, 30].

Phase 3—**Pilot test of the preliminary instrument** - A pilot study will be conducted to determine whether the DCE instrument is appropriate for the main investigation. As described above, an electronic form will be created for the final version. However, specific questions about the difficulty level and the time needed to answer the questions in each block will be inserted after each choice set. For this purpose, no pre-set sample size is required [17]. A minimum convenience sample of 10 dentist volunteers is foreseen, but depending on the observations, more respondents can be included in this phase. Besides completing the form, the pilot respondents will be invited to share their difficulties and opinions with the coordinator board to create suggestions for improvement for the experiment. In case the pilot instrument is acceptable and does not need adjustments, this sample will be considered automatically as part of the main sample - an internal pilot study [31, 32]. In case of amendments are needed, and a change in the instrument or the experimental design is mandatory, an external pilot will be considered [32].

Phase 4—**Adjustments in the preliminary instrument –** Based on inputs of the pilot respondents regarding cognitive exhaustion, reasonability and comprehensibility of the tests, any amendment may be done in the attributes and levels, number of alternatives, experiment format or presentation. Depending on the type of the request/query, one or more phases described above will have to be redone, and eventually, a new pilot study may be necessary to retest the changes and produce a final experiment to be tested in the whole main sample.

